## 1. Background

In the last years there were revolutionary findings (i.e. thrombectomy) and an accumulation of a significant amount of evidence-based knowledge about acute stroke therapy and stroke prevention, but there is still a paucity of evidence-based knowledge about recovery and rehabilitation, although the evidence base for stroke rehabilitation has grown exponentially in the last 20 years. Stroke is the major cause for permanent disability in adults. Unilateral motor weakness is one of the most common deficits resulting from stroke and one of the main causes of disability. It is still unclear, which physiotherapeutic approaches in stroke rehabilitation are most effective. The Bobath-concept is one of the most widely used approaches in stroke rehabilitation within the western world, although several studies have failed to demonstrate superiority and showed partially even inferiority compared to other physiotherapy approaches.

Modern approaches follow the idea, that functional improvement to a large extent relies on the use of compensatory movement strategies, enabling patients to learn to cope with their deficits. The Vojta therapy is based on a completely different approach: the reflex locomotion. Vojta described inborn movement sequences of reflex locomotion that are retrievable at all times. The therapist stimulates this innate patterns of movement by applying pressure to defined zones. There are ten zones available on the body, the arms and legs. The therapeutic use of reflex locomotion enables elementary patterns of movement in patients with impaired locomotor system, for example due to brain damage by stroke, to be restored once more, assuming that repeated stimulation of these “reflex-like” movements can lead to something like “new networking” within functionally blocked neuronal networks. After Vojta treatment, these patterns are more spontaneously available to the patient. Clinical experience shows, that Vojta therapy improves postural control, uprighting against gravity and goal-directed movements.

Initially Vojta therapy was applied mostly for newborns with central coordination disorders or spastic movement disorders. Although Vojta reflex locomotion is a sufficient therapeutic method for the promotion of normal posture control and the direct activation of respiratory muscles in children with cerebral palsy, its application in other diseases has not been well studied. Vojta reflex locomotion has been reported to activate the trunk muscles and the deep muscles of the spine to regulate trunk stability and increase spinal rotation force, thereby enhancing postural control ability. Nowadays it is also widely-used in adults, but concerning neurological diseases there is only some evidence for patients with multiple sclerosis (indicating a positive effect of Vojta therapy) and for patients with paraplegia. However to date no study has been performed for stroke.

Most studies on stroke recovery and neurorehabilitation have been conducted in so-called chronic patients, with stroke onset more than 6 months before, probably because this patients are easier to recruit and have a stable baseline, so that changes in performance can be

attributed to the experimental treatment. Only few recovery trials have initiated restorative treatments within 7 days after onset and can therefore be classified as acute. There is an ongoing debate about the optimal timing of rehabilitation, although starting rehabilitation early is a widely accepted principle of care for people affected by stroke. Delays to the initiation of rehabilitation seem to be associated with a poorer outcome and a longer length of stay in hospital for patients, furthermore motor training started around 5 days after stroke is more effective than training started at day 14 or day 30.

The fact that there is a limited time window for the greatest motor recovery and increased receptivity to training regimens after injury is congruent with observations in animal models suggesting that there is about a month of heightened plasticity in the brain early after stroke when most recovery from impairment occurs. For this reason in our trial we investigate acute stroke patients within 72 hours after stroke onset.

## **2. Purpose:**

In our hospital we introduced Vojta therapy in 2013 on the stroke unit within the established treatment concept (predominantly Bobath concept). We observed that Vojta therapy improved efficacy of other approaches, working with repetitive exercises by activation of automatic movement patterns and lead to an improvement of postural control, uprighting against gravity and goal-directed movements. Directly after Vojta therapy stroke patients showed an improvement of the posture and movement patterns, that showed definable consolidation tendency after a few days on the stroke unit. As an early effect we observed muscle fasciculation in the motoric target area -even in plegic limbs, appearance of movement sensation in neglect regions, as soon as vegetative (piloerectile, vasomotoric, sudomotoric) reactions in the therapeutic area. Patients reported of sensoric effects as a heat sensation projected to the periphery, suggesting a systemic effect of Vojta therapy. This observations motivated us to further investigate Vojta therapy in stroke rehabilitation.

We designed a randomized clinical trial (RCT) to compare Vojta therapy and conventional physiotherapy in patients with acute ischemic (AIS) or hemorrhagic stroke (ICH). This RCT will be the first trial to investigate improvement of postural control due to Vojta therapy in early rehabilitation of stroke patients, which is a very new approach in stroke-rehabilitation. The aim of the trial was to investigate Vojta therapy in acute stroke patients with severe hemiparesis patients within 72 hours after onset.

## **3. Hypothesis:**

We hypothesise, that Vojta therapy improves postural control and motor function in early rehabilitation of stroke patients compared to conventional physiotherapy.

## **4. Study Design:**

This is an investigator-initiated, prospective parallel-group, single-center, randomised controlled trial and will be conducted in the Department of Neurology at Frankfurt Höchst Hospital, Frankfurt, Germany. Patient recruitment and treatment will be performed by specifically trained personnel on a certified stroke unit (for more details about certification please see <http://www.dsg-info.de>). All data will be monitored from clinical files as source documents by the principal investigator.

## 5. Eligibility

### 5.1 Inclusion Criteria:

- Adult patients (> 18 years)
- CT or MRI proven acute ischemic (AIS) or hemorrhagic stroke (ICH) within 72h after onset of symptoms
- Severe hemiparesis (medical research council scale for muscle strength  $\leq 2$ )
- premorbid modified Rankin Scale (mRS)  $\leq 3$
- maximum National Institute of Health Stroke Scale Score (NIHSS) 25
- Voluntary written consent by the patient

### 5.2. Exclusion Criteria:

- Severe cognitive impairment due to aphasia or dementia, prohibiting that physiotherapeutic challenges can be understood.
- Participation on another clinical trial
- Pregnancy

## 6. Screening and Randomisation:

All potentially eligible patients are screened on the first day after admission to the stroke unit and during the first 72h after stroke onset, in case of deterioration after admission. Eligible patient with written informed consent will be enrolled and randomly assigned (1:1) to receive usual stroke unit care with conventional physiotherapy (control group) or Vojta therapy (interventional group).

| Arm                  | Therapy                    |
|----------------------|----------------------------|
| interventional group | Vojta therapy              |
| control group        | conventional physiotherapy |

Randomisation will be performed with sealed, opaque and sequentially numbered envelope. The investigators are instructed to assign the patient according to the envelope with the lowest randomisation number. Randomisation has to be done within 72 hours after onset of symptoms or after patients were last seen well and can be done by a physiotherapist or the investigator, who enrolles the subject. Stratification for stroke severity was disclaimed due to the small sample size.

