## **11 Sample size and statistical analysis plan:**

### 11.1 Sample size

This is a pilot trial. Vojta therapy has never been investigated in stroke patients. A sample size calculation for this pilot trial was not feasible, because desired parameters, as the estimated effect size or the standart deviation due to missing prior information or data in the literature could not be estimated. For feasability reasons we choose a sample size of 40 subjects (20 in each group) in order to complete recruitment in this monocentric trial within one to 1,5 years.

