### 11.2 Statistical analysis plan

We plan an intention to treat analysis. For the primary endpoint (difference of scores in trunc control test between day 9 and baseline) an increase of 12 points (=12%) on the scale of the TCT was predefined as a meaningful difference pragmatically, due to lack of data in the literature, because an improvement of 12 points in the TCT indicates a clinical relevant improvement of self-dependence (i.e. no more need of an auxiliary person, no more need for an adjuvant as edge of bed for moving). Normal distribution of the variables will be tested by the Shapiro-Wilk-test. For the primary endpoint we assume non-Gaussian distribution and we plan an analysis of variance with the non-parametric Mann–Whitney-U-test. The primary endpoint (difference of scores in trunc control test between day 9 and baseline) will be tested concerning the influencing factors a priori known to potentially affect outcome (age, sex, NIHSS > or <10 at baseline; stroke site, thrombolysis and thrombectomy) to test whether they affected the treatment. Complications occurring between baseline and day 9 will be analyzed with the exact Fisher Test. An interim analysis is not planned. We have not defined any discontinuation criteria. Statistical analysis will be made by the principal investigator with support of a statistical institute.

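### Small sample size is a poor reason to decline stratifying for stroke severity, and the primary Mann-Whitney test also leaves severity out; a severity-adjusted primary analysis would recover some precision at little cost.

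*Protocol*

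**What the plan says.** Section 4 describes a "prospective parallel-group, single-center, randomised controlled trial". Section 6 has patients "randomly assigned (1:1) to receive usual stroke unit care" with either conventional physiotherapy or Vojta therapy. On the mechanism it says "Randomisation will be performed with sealed, opaque and sequentially numbered envelope", and describes no blocks, strata or minimisation. It adds: "Stratification for stroke severity was disclaimed due to the small sample size". No other reason is given.

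Section 11.1 states: "For feasability reasons we choose a sample size of 40 subjects (20 in each group"), after "A sample size calculation for this pilot trial was not feasible".

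Section 11.2 names a Mann-Whitney U test on the change in TCT from baseline to day 9 as the primary analysis, and calls 12 points meaningful. It then says that the primary endpoint will be examined for "influencing factors a priori known to potentially affect outcome (age, sex, NIHSS > or <10 at baseline", together with stroke site, thrombolysis and thrombectomy. It does not say that the treatment comparison is adjusted for any of them.

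Eligibility (Section 5.1) allows a "maximum National Institute of Health Stroke Scale Score (NIHSS) 25". Table 2 records NIHSS at screening and again at Test 1, so a severity score exists before allocation.

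**The concern.** The reason in Section 6 points the wrong way. As a trial grows, simple randomisation evens out severity on its own; at 20 per arm it often does not. A small sample is a good argument against many strata, because most blocks would stay incomplete. It is a weak argument against one two-level factor at one centre.

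The protocol itself names NIHSS as a factor that may affect outcome, yet neither the allocation nor the primary test uses it. If severity does influence TCT change, its between-patient variation stays in the error of the primary comparison, and an unlucky allocation shifts the observed difference. In a 40-patient trial, where Section 7 says the assessors of the primary outcome know the allocation, an evident severity imbalance would also make the result harder to interpret.

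**Working it through.** **Plan's own figure.** The total of 40 was chosen for feasibility. There is no alpha, power or SD behind it, so there is nothing to reproduce.

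**Step 1: chance imbalance.** From the protocol: N = 40, 20 per arm. Assumed: K severe patients among the 40, as the documents give no share. If k of them fall in one arm, the gap in proportions is (2k − K)/20, and k is hypergeometric:

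P(gap ≥ 20 points) = Σ C(K,k)·C(40−K, 20−k)/C(40,20), over |2k − K| ≥ 4.

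| K (share severe) | gap ≥ 20 points | gap ≥ 30 points |
|---|---|---|
| 12 (30%) | 30.1% | 8.2% |
| 16 (40%) | 33.3% | 10.5% |
| 20 (50%) | 34.3% | 11.3% |
| 24 (60%) | 33.3% | 10.5% |

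With half severe, the chance of a gap of at least 20 points falls to 7.1% at N = 100, 0.7% at N = 200 and practically zero at N = 400. The risk is therefore greatest at this trial's size.

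These figures hold for exact 20:20 arms and an even K, for which a gap of exactly 20 points can occur. When the number of severe patients was itself random, with an expected share of 30% to 70%, simulation gave 22% to 27% for unstratified blocks of 4 and 18% to 22% for simple randomisation. The risk is lower but still substantial.

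**Step 2: what a gap does.** Assume that severity shifts TCT change by 20 points (range 10 to 30). A 30-point gap then moves the group difference by 0.30 × 20 = 6 points (range 3 to 9), against the 12 points called meaningful.

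With half severe, Var(k) = 20 × 0.5 × 0.5 × 20/39 = 2.56, so the SD of the gap is 2 × 1.60/20 = 0.16. It contributes 0.16 × 20 = 3.2 points. With residual SD 15, the remaining error is 15 × √(2/20) = 4.74. Together: √(4.74² + 3.2²) = 5.7 points, against about 4.7 if severity were balanced or adjusted for.

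**Step 3: power for 12 points.** Assumed: 20 per arm, two-sided 5%, half severe, normal residuals. The simulated columns compare unstratified allocation with the planned Mann-Whitney test and with a severity-adjusted analysis. At 4,000 runs the Monte Carlo error is about √(0.5 × 0.5/4000) = 0.8 points.

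The last column is a hand check, Φ(12/(S·√(2/20)) − 1.96). Here S = √(SD² + effect²/4) without adjustment and S = SD with it.

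| Severity effect, residual SD | Planned test | Adjusted | Hand check (S; power) |
|---|---|---|---|
| 20, 15 | 49% | 68% | 18.0; 56% → 15; 72% |
| 10, 15 | 62% | 68% | 15.8; 67% → 15; 72% |
| 20, 25 | 26% | 31% | 26.9; 29% → 25; 33% |
| 10, 25 | 30% | 31% | 25.5; 32% → 25; 33% |

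The normal approximation runs a few points high throughout, but it shows the same pattern: a large gain in the first row, and little in the others.

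**Step 4: which change produces the gain.** In the first scenario the planned test has about 49% power whether or not allocation is stratified. Adjustment brings it to about 68% without stratification, and stratification adds about 0 to 2 points more. Type I error of the unstratified Mann-Whitney test is about 5%. With stratified allocation and the test left unadjusted it is about 2%.

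**The case against.** Four points weigh on the other side.

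**Validity.** A reader might infer that the trial is biased without stratification. It is not. Randomisation keeps the test valid, and chance imbalance is already part of its error rate.

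**Source of the gain.** A reader might also infer that stratifying the envelopes would lift power from about half to more than two thirds. Step 4 shows otherwise: the gain comes from the analysis. Blocked lists in two strata also have a price. Treatment is open, and a physiotherapist or the enrolling investigator may randomise, so short lists make the next allocation easier to guess.

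**Size.** The documents give neither the effect of severity on TCT change nor its SD. TCT is bounded at 0 and 100 and scored in coarse steps, so the direction of the effect is not certain either. Section 11.2 says only that the factors may affect outcome. Eligibility also narrows severity, through severe hemiparesis and the NIHSS ceiling. The largest gain needs a large effect together with a small SD.

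**Existing plans.** Section 11.2 does intend to examine the primary endpoint against NIHSS, so severity is not ignored altogether, and a separate analysis plan may say more. Nor does the protocol say that the secondary outcomes are unadjusted; it gives no method for them. The trial is also a declared pilot.

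All of this limits the point without removing it. The stated reason is still unsound, and the primary test as named still takes no account of severity. Examining factors alongside it is not an adjusted treatment estimate.

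**Conclusion.** The point holds as one about precision and about an unsound rationale. Small size does not justify declining a single two-level factor: the chance of a gap of at least 20 percentage points is 30% to 34% at 20 per arm if 30% to 60% of patients are severe, given equal arms and an even number of severe patients. The planned analysis remains valid.

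Adjusting the primary analysis for severity gains between about 1 and 19 points of power for a 12-point difference across the four scenarios. Only the most favourable one gives a large gain; the other three give 1 to 6 points. All rest on assumed severity effects, SDs and an even split of severity. The documents do not support a claim that the trial must stratify its allocation.

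**What to change.** **Section 11.2.** Make a prespecified severity-adjusted comparison the primary analysis in place of the unadjusted Mann-Whitney test. Either a van Elteren test stratified by pre-treatment NIHSS or a rank ANCOVA on pre-treatment NIHSS would serve. State which pre-treatment value is used (screening or Test 1). If NIHSS is categorised, assign a score of exactly 10 to one side, because the present cut leaves it in neither. A van Elteren test with two strata may gain somewhat less than the adjusted figures in the table.

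**Section 6.** Delete the small-sample reason.

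The cost is one analysis term and two edited sentences, using a score already collected.

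**Optional.** Allocation could be stratified by screening NIHSS in two levels, with a second set of envelopes and concealed blocks of varying size. In 60,000 simulated trials with blocks of 4 in two strata, no gap exceeded 10 percentage points and arm sizes stayed between 18 and 22. The main benefit is preventing a visible imbalance; the cost is more predictable allocation in an open trial. If adopted, it must be paired with the stratified analysis, since the unadjusted test would then be conservative (type I error about 2%).

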## 7. Masking:

Masking of treatment is not possible because of the different appearance of the two physiotherapeutic approaches. Blinded assessment meanwhile hospital stay is not feasible, because it cannot be ensured that assessments are conducted by an evaluator physical therapist different from the treating physical therapist, due to logistic reasons. The trial is observer blinded only for the secondary clinical outcome Barthel Index and modified Ranking Scale at day 90. All other outcome assessors will have knowledge of the interventions assigned to individual participants.

## **8. Predefined Outcome Measures**

### **8.1. Primary Outcome Measure:**

Improvement of postural control measured with the trunc control test (TCT) on day 9 after admission to the hospital compared to baseline (Difference in scores on TCT scale between baseline and day 9)

### **8.2. Secondary Outcome Measures:**

(i) Improvement of neglect measured with the Catherine Bergego Scale (CBS) part 5 and 6 on day 9 after admission to the hospital compared to baseline (Difference in scores on CBS scale between baseline before treatment and day 9 after treatment)

(ii) Improvement of arm motor function measured with the motor evaluation scale for upper extremity in stroke patients (MESUPES, part 1 to 4) on day 9 after admission to the hospital compared to baseline (Difference in scores on MESUPES between before treatment and day 9 after treatment).

(iii) Improvement of stroke severity measured with the National Institute of Health Stroke Scale (NIHSS) on day 9 after admission to the hospital compared to baseline (Difference in scores on NIHSS between baseline before treatment and day 9 after treatment).

(iv) Improvement of the Barthel Index (BI) on day 9 after admission to the hospital compared to baseline (Difference in scores on BI between baseline before treatment and day 9 after treatment)

(v) Improvement of the modified Rankin Scale (mRS) on day 90 after stroke compared to baseline (Difference in scores on mRS between baseline before treatment and day 90). The 90 day mRS is assessed via telephone interview by a blinded assessor.

(vi) Improvement of the Barthel Index (BI) on day 90 after stroke compared to baseline (Difference in scores on BI between baseline before treatment and day 90). The 90 day BI is assessed via telephone interview by a blinded assessor.

(vii) Improvement of the neglect (measured with the Catherine Bergego Scale) before and after every single intervention on day 2, day 5 and day 9.

(viii) Improvement of arm motor function (measured with the MESUPES) before and after every single intervention on day 2, day 5 and day 9.

The timing for the primary endpoint was chosen at day nine, because this is the mean residence time of stroke patients in the acute clinic before discharge to a rehabilitation center.

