## 9. Timeframes for Visits Outcome Measures

- Randomisation: Maximum 72h after stroke onset
  - Test 1: on day 2 after admission to hospital (+/- 1 day)
  - Test 2: on day 5 after admission to hospital (+/- 1 day)
  - Test 3: on day 9 after admission to hospital (+/- 1 day)
  - Test 4: on day 90 after stroke onset (+/- 5 days)
- The trunc control test (TCT) will be assessed at day 2 after admission to hospital before the first treatment (baseline), at day 5 and day 9 after treatment.
  - The National Institutes of Health Stroke Scale (NIHSS) will be assessed at day 2 after admission to hospital before the first treatment (baseline) and at day 9 after treatment.
  - The Catherine Bergego Scale (CBS) and the Motor Evaluation Scale for Upper Extremity in Stroke Patients (MESUPES) will be assessed at day 2, day 5 and day 9 after admission before and after treatment.
  - The modified Rankin Scale (mRS) and the Barthel Index (BI) will be assessed at day 2 after admission to hospital before the first treatment (baseline), at day 9 after treatment and at day 90 after stroke onset via a phone interview.
  - Investigators will record the occurrence of any serious adverse event and other safety outcomes that occur during hospital admission up to day 90.

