**(v) Modified Rankin Scale (mRS)  :**

The modified Rankin Scale is a single-item global outcomes rating scale that categorises level of functional independence with reference to pre-stroke activities and is an ordinal scale ranging from 0 (*no symptoms*), 1 (*no significant disability despite symptoms; able to carry out all usual duties and activities*), 2 (*slight disability: unable to carry out all previous activities but able to look after own affairs without assistance*), 3 (*moderate disability: requiring some help, but able to walk without assistance*), 4 (*moderately severe disability: unable to walk without assistance, and unable to attend to own bodily needs without assistance*), to 5 (*severe disability: bedridden, incontinent, and requiring constant nursing care and attention*), with a score of 6 allocated to those who die. Assessment is carried out by asking the patient about their activities of daily living, including outdoor activities.

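### The masked day-90 mRS is defined as a difference from an unmasked day-2 rating, so deaths are ordered by starting level and baseline rating error carries through

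*Protocol*

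**What the plan says.** Section 8.2 lists eight secondary outcomes. Item (v), the 90-day mRS, is fixed as "Difference in scores on mRS between baseline before treatment and day 90". Item (vi) uses the same form for the Barthel Index: "Difference in scores on BI between baseline before treatment and day 90". For the day-90 half of (v) the section adds: "The 90 day mRS is assessed via telephone interview by a blinded assessor".

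Section 7 states: "The trial is observer blinded only for the secondary clinical outcome Barthel Index and modified Ranking Scale at day 90". It continues: "All other outcome assessors will have knowledge of the interventions assigned to individual participants".

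Section 9 gives the timing. The mRS and BI "will be assessed at day 2 after admission to hospital before the first treatment (baseline), at day 9 after treatment and at day 90". Table 2 puts this baseline under Test 1, the column after enrolment and randomisation. The premorbid mRS and a first NIHSS are listed separately, under screening.

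Section 10.1 (v) describes the mRS as an ordinal scale that "categorises level of functional independence with reference to pre-stroke activities", "with a score of 6 allocated to those who die". Section 10.1 (vi) gives the BI a range of 0 to 20.

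**The concern.** The scale already has a place for death: 6, below every living state. Subtracting a starting value removes that property, because the same day-90 state gets a different score depending on where the patient began. In severely paretic patients (MRC grade 2 or less, NIHSS up to 25, section 5.1), deaths before day 90 are a realistic event, and section 8.3 provides for them.

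The second issue is masking. The day-90 telephone ratings are the only outcomes free of knowledge of the arm. Expressing them as differences adds a rating that section 7 leaves unmasked. At stake is how clean the trial's best-protected evidence is, not its primary result.

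**Working it through.** **Inputs.** mRS 0 to 6 with death = 6 (section 10.1 (v)); outcome = difference between baseline and day 90 (section 8.2 (v)); 20 patients per arm (section 11.1). The protocol states no figure for this outcome that could be reproduced: no expected distribution, mortality, effect size or standard deviation.

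**Step 1: ordering of deaths.** Take improvement = baseline mRS - day-90 mRS, so that higher is better.

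| Baseline | Day 90 = 0 | 1 | 2 | 3 | 4 | 5 | Death (6) |
|---|---|---|---|---|---|---|---|
| 3 | 3 | 2 | 1 | 0 | -1 | -2 | -3 |
| 4 | 4 | 3 | 2 | 1 | 0 | -1 | -2 |
| 5 | 5 | 4 | 3 | 2 | 1 | 0 | -1 |

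Reading across rows:
- Death from 5 (5 - 6 = -1) ties with survival at 5 from 4 (4 - 5 = -1) and with survival at 4 from 3 (3 - 4 = -1).
- Death from 5 (-1) ranks above survival at 5 from 3 (3 - 5 = -2).
- Death from 4 (4 - 6 = -2) ties with survival at 5 from 3 (-2).
- Death from 5 (-1) ranks above death from 4 (-2).

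The first tie and the unequal deaths need only baselines of 4 and 5. The other cases need a baseline of 3, which the eligibility criteria do not exclude but which may be rare with severe hemiparesis. The protocol names no test for this outcome, but the ordering is built into the difference and holds for any test of the difference alone, rank tests included.

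**Step 2: baseline error.** If the recorded baseline = true baseline + e, then recorded improvement = true improvement + e. The error passes through with coefficient 1, although the day-90 state is unchanged. The same holds, with the sign reversed, for BI.

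**Step 3: illustration of size, on assumed inputs only.** A simulation with no treatment effect used 20 per arm, a two-sided 5% Mann-Whitney test, 10% mortality and 3000 runs. A share of one arm was rated one level worse at baseline, capped at 5. Baseline mixes (mRS 3/4/5) were assumed.

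| Share misrated | False-positive rate, mix 5/35/60% | False-positive rate, mix 10/60/30% |
|---|---|---|
| 0 | 0.050 | 0.039 |
| 25% | 0.058 | 0.062 |
| 50% | 0.071 | 0.117 |
| 100% | 0.146 | 0.342 |

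Analysing the day-90 mRS itself gave 0.043 to 0.056 in every scenario. The simulation error is about √(0.05 × 0.95 / 3000) = 0.004. Because patients at 5 cannot be rated worse in life, a 25% misrating shifts the mean by only 0.25 × 0.40 = 0.10 levels in the first mix and 0.25 × 0.70 = 0.175 in the second (simulated 0.094 and 0.179).

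**The case against.** The case against is strongest on masking. The baseline is taken before the first treatment (section 9). Assessments are made by two physiotherapists, one from each group, with a third if they disagree (section 12.1). Those rating the mRS should be certified (section 12.4). These steps work against a one-directional error in one arm. The windows for enrolment (days 1 to 3) and Test 1 (day 2 ± 1) overlap, so the claim that the rater knows the arm at baseline rests on the column order of Table 2 and the general sentence in section 7. A reader might infer that the definition brings rater bias into the result. The documents do not support that: they show an unmasked component, not a bias. In the illustration a 25% misrating moves the false-positive rate very little, and no share of misrated patients has a source in the protocol.

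A reader might also infer that the BI comparison is confined to survivors. The protocol gives no BI value for death, but such a rule may stand in an analysis plan that is not shown, and section 11.2 plans intention to treat. That silence is not a fault.

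Finally, if nearly all patients start at 4 or 5, the difference follows the day-90 score closely, and misordering is limited to deaths and survivors who worsen. Deaths are also evaluated separately under section 8.3. This limits the practical effect, but it leaves the ordering problem untouched, because that follows from the definition.

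**Conclusion.** The point holds for the definition of outcome (v). As a difference, the mRS no longer keeps death as the worst result: deaths score -1 or -2 from baselines of 5 or 4, and a death can tie with or rank above a survivor. This needs no assumption beyond the protocol's own scale and definition. How many comparisons it would affect depends on mortality and the baseline distribution, neither of which is given.

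The unmasked baseline in (v) and (vi) is a possible route to bias, reduced but not removed by paired raters and pre-treatment timing. Its size cannot be derived from the document, and the simulated rates show sensitivity under assumed inputs only.

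These are two of eight secondary outcomes in a 40-patient pilot, and the primary Trunk Control Test comparison is unaffected. The change is worth making because it is cheap and protects the only masked ratings.

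**What to change.** - **(v):** define the outcome as the observed day-90 mRS, 0 to 6 with death = 6, compared between arms on the full ordinal scale. Name one method in advance: an unadjusted Mann-Whitney test, or a proportional odds model adjusted for the premorbid mRS and the NIHSS recorded at screening. The standard Mann-Whitney test takes no covariates, so the two should not be combined.
- **(vi):** define the outcome as the observed day-90 BI in a rank-based comparison, with deaths ranked below every survivor. Giving deaths a BI of 0 would tie them with living patients at 0. Do not correct with the Test 1 BI, which is itself an unmasked rating.
- Change from baseline may stay as a descriptive summary for both.

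Cost: two definitions are reworded, and they no longer match the change format of the day-9 outcomes. Every value needed is already in the trial schedule.
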